## Abstract

It is crucial for human health that the immune system of the gastrointestinal tract works effectively. Dietary modulation is one of the factors that regulate the immune response in the gut. This study aims to develop a safe human challenge model to study gastrointestinal inflammation and immune function. This study focuses on evaluating gut stimulation induced by the oral cholera vaccine in healthy people. In addition, this paper describes the study design for assessing the efficacy and safety of a probiotic lysate, identifying whether functional ingredients in food can modulate inflammatory response induced by oral cholera vaccine. Forty-six males aged 20 to 50 with healthy bowel habits will be randomly allocated to the placebo or intervention group. Participants will consume 1 capsule of probiotic lysate or placebo twice daily for 6 weeks, take oral cholera vaccines on visit 2 (day 15) and visit 5 (day 29). The level of fecal calprotectin, a marker of gut inflammation, will be the primary outcome. The changes of cholera toxin-specific antibody levels and local/systemic inflammatory responses will be evaluated in blood. The purpose of this study is to evaluate gut stimulation of the oral cholera vaccine and investigate the effect of a probiotic lysate on improving the mild inflammatory response induced by the vaccine or supporting the immune response in healthy subjects.

**Trial registration**: * This trial is registered in the International Clinical Trials Registry Platform of WHO (ICTRP, registration number: KCT0002589).

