### Outcome measures

Outcomes related to efficacy and safety will be evaluated. Trained investigators and research coordinators will conduct interviews and blood sampling of subjects. Participants will be instructed to visit after a 12-hour overnight fast on each visit. The vaccination time points are fixed on day 15 and day 29. On the day of taking the vaccine, blood must be collected before providing the vaccine. Fecal samples will be collected on days 0, 14, 16, 17, 28, 30, 31, and 42 at the subjects’ homes. Fecal sampling will be allowed on day 1 or day 43, respectively, when it is difficult to collect samples on day 0 or day 42. If subjects cannot collect a fecal sample on day 0 or day 1, they will collect a fecal sample as soon as possible and start intake of the study product the day after collecting the first fecal sample. The stool sample is frozen in the home freezer and can be submitted with ice packs the next day or delivered to the laboratory within an hour through the delivery system provided.

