### Statistical analysis

Data analyses will be performed with intention-to-treat subject data (all data from subjects who have received the study product) or per-protocol subject data (only data from subjects who completed the study at least 80% compliant with the study product). Variables will be tested for normal distribution and data transformation will be performed on skewed variables. Parametric or non-parametric analyses (dependent on the outcome of the distribution of data) such as paired *t*-test, Student’s *t*-test, or Wilcoxon signed-rank test will be used to analyze the difference within each group or between the groups for continuous variables. Chi-square or Fisher’s exact test will be used to analyze the difference between the groups for categorical variables. A linear mixed-effects model with group and time as fixed effects and subject as the random effect will be applied to compare the changes between groups over the intervention period. The correlation between variables will be analyzed by Pearson’s correlation or Spearman correlation and regression analysis will be performed. The data will be analyzed using the SAS 9.4 statistical software. The difference between the groups will be tested two-sided for all study outcomes. *P*-values <0.05 are classified as statistically significant.

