In this study, we describe clinical trials which will evaluate the effect of *Lb*. *plantarum* lysate on the inflammatory response or on the immune response, suggesting the protocol that the oral cholera vaccination can be used as a model to induce a mild inflammatory response in the gut. Oral cholera vaccinations are used to induce an immune response in the intestine to prevent cholera infection. However, oral vaccines can also affect the immune response of other mucosal tissues. Oral vaccination primarily interacts with the immune system through the oral cavity to the small intestine and induces the expression of vaccine-specific IgA in gastrointestinal and tissue-specific homing of B cells and T cells [28]. The aim of the measurement of cholera toxin-specific IgA was to evaluate whether oral cholera vaccination is able to induce potent IgA responses in serum.

We hypothesized first, the oral cholera vaccination will induce a significant increase in the gut inflammatory response in the gastrointestinal tract, and second, *Lb*. *plantarum* K8 lysate will significantly improve the inflammatory response or support the immune response induced by oral cholera vaccination in healthy male subjects. To our knowledge, this is the first randomized, double-blind study to investigate the efficacy of *Lb*. *plantarum* lysate on the inflammatory response as induced by oral cholera vaccination. We expect that the results of this study will contribute to the scientific evidence that the tested probiotic lysate has the potential of modulating intestinal inflammation induced by the oral cholera vaccine or improving the immune response.

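### As written, the mixed model has no group-by-time term or baseline adjustment, so its group coefficient is an average level difference and not the difference in change it is meant to compare

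*Protocol article*

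**What the plan says.** All references are to the protocol article.

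- **Model (Statistical analysis).** "A linear mixed-effects model with group and time as fixed effects and subject as the random effect will be applied". Its stated purpose is "to compare the changes between groups over the intervention period". The article mentions no group-by-time interaction, baseline covariate or change-from-baseline response.
- **Other between-group tests (same section).** Student's t-test and non-parametric tests are listed for differences within or between groups. The section does not say whether they apply to levels or to changes, or at which time point.
- **Hypothesis (Discussion).** The second hypothesis is that "K8 lysate will significantly improve the inflammatory response or support the immune response induced by oral cholera vaccination".
- **Primary outcome (Abstract).** "The level of fecal calprotectin, a marker of gut inflammation, will be the primary outcome".
- **Sampling (Outcome measures).** "Fecal samples will be collected on days 0, 14, 16, 17, 28, 30, 31, and 42", and "The vaccination time points are fixed on day 15 and day 29". The Interventions section has product taken on days 1 to 43.

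**The concern.** A difference in change between two groups is a group-by-time quantity. A model for levels with group and time as separate terms has one constant group difference and one time course shared by both groups. It assumes that the profiles are parallel, so no parameter represents a difference in change.

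The lysate hypothesis is about the response to vaccination. Day 0 precedes product and vaccine, so no effect can appear there. Day 14 precedes the vaccine, so no effect on the vaccine response can appear there either. Both samples still enter the group coefficient with full weight. Two things follow:

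- an effect on the vaccine response is diluted;
- any day 0 difference that arose by chance stays in the estimate, because nothing adjusts for it.

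**Working it through.** **Inputs from the article.** Eight fecal samples per subject; vaccine on days 15 and 29; two-sided testing at 0.05; 19 per group (Sample size calculation); calprotectin SD 20 μg/g.

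**Assumptions.** Complete data, equal variance σ² at each sample, a common within-subject correlation ρ (0.5, with 0.3 and 0.7 as the range), and a constant effect δ on the affected samples. The article gives neither ρ nor δ for the lysate.

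The point concerns no figure stated in the plan. The 19 per group serves only as an input. It was not reproduced: a paired t-test for 15 to 50 μg/g with SD 20 at 90% power needs 5 to 10 subjects for ρ between 0.75 and 0. That is a separate matter.

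**Step 1: dilution.** In balanced data the additive random-intercept test of group equals a t-test on subject means over the eight samples. If k of the 8 samples carry the effect, the coefficient estimates (k/8)δ.

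- Days 16, 17, 30, 31: 4/8 = 0.50
- All post-vaccine samples (adding 28 and 42): 6/8 = 0.75
- All samples after day 0 (adding 14): 7/8 = 0.875

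**Step 2: power of the additive group term.** The variance of a subject mean is σ²[ρ + (1−ρ)/8]. At ρ = 0.5 this is 0.5625σ², so the standard error of the group difference is 0.75σ × √(2/19) = 0.243σ, with 36 df. For δ = 1σ the noncentrality is 0.50/0.243 = 2.06, 0.75/0.243 = 3.08 or 0.875/0.243 = 3.60.

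**Step 3: power of a day-0-adjusted contrast on the k affected samples.** The residual variance is σ²[ρ + (1−ρ)/k − ρ²]. At ρ = 0.5 and k = 4 this is 0.375σ², so the standard error is 0.612σ × √(2/19) = 0.199σ and the noncentrality is 1/0.199 = 5.03, with 35 df. For k = 6 and 7 the noncentrality is 5.34 and 5.44.

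**Step 4: the overall interaction test (7 and 252 df).** The noncentrality is (19/2) × Σ(δₜ − mean δ)² / [(1−ρ)σ²], which is 38.0, 28.5 and 16.6 for k = 4, 6, 7.

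| Effect present on (δ = 1σ, ρ = 0.5) | Coefficient / true effect | Additive group term | 7-df interaction F | Day-0-adjusted contrast |
|---|---|---|---|---|
| days 16, 17, 30, 31 | 4/8 | 52% | 99.8% | 99.8% |
| six post-vaccine samples | 6/8 | 85% | 99% | 99.9% |
| seven samples after day 0 | 7/8 | 94% | 85% | over 99.9% |

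**Sensitivity.** With ρ = 0.3 the additive power is 67%, 95% and 99%. With ρ = 0.7 it is 42%, 75% and 86%. The adjusted contrast stays above 99% throughout. With δ = 0.5σ and ρ = 0.5, the additive term has 17%, 32% and 42%, and the contrast 69%, 74% and 75%.

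**Step 5: day 0 imbalance.** The standard error of the day 0 group difference is √(2/19) = 0.324σ, or 20 × 0.324 = 6.5 μg/g. Given a day 0 difference b and no lysate effect, the additive coefficient has expectation b(1 + 7ρ)/8. At ρ = 0.5 this is 0.5625b. A chance imbalance of one standard error therefore moves the estimate by 0.5625 × 6.5 = 3.7 μg/g.

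**The case against.** **The wording may be shorthand.** The sentence does not say main effects only and does not exclude an interaction. Its stated purpose implies one, and a condensed article may name the factors and leave the rest to the full protocol or SAP. This stands. The problem may lie in the reporting and not in the intended analysis, but the published sentence would still need the same correction.

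**Changes could be compared in other ways.** If the response were change from day 0, the group term would test an average difference in change, at 4/7 of an effect confined to four samples. The listed t-tests could also be applied to change scores. Both are possible, but the article states neither, and the mixed model is the only method that it assigns to comparing changes between groups. A reader might infer that the trial cannot test the lysate hypothesis at all. The article does not support that.

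**Half the effect is one end of a range.** A reader might take 4/8 and 52% as the cost of the wording. That requires no effect on days 14, 28 and 42. Product is taken throughout days 1 to 43, and no section limits the response to two days after each dose. Only day 0 is necessarily free of any product effect. The fractions also do not apply to antibodies, which are measured on a different schedule.

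**The power gap is not due to the interaction alone.** The adjusted contrast differs from the additive term in three ways: the interaction, the day 0 adjustment and the choice of days. This stands. With an effect on all seven later samples, the 7-df interaction test (85%) does worse than the additive term (94%).

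**Type I error.** A reader might infer that baseline imbalance inflates the false-positive rate. Randomization keeps it at 5% overall; in simulations with no effect the group term rejected in 4.3% to 5.0% of runs. The harm is a less precise estimate that leans with whatever imbalance occurred.

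**Conclusion.** The concern holds for the sentence as published. Fitted literally to levels, the model does not estimate the quantity it is assigned to compare, and nothing else in the article supplies the interaction, the baseline adjustment or a change-score response.

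The loss depends on how long the effect lasts. At 1 SD and correlation 0.5, power is 52% to 94%, against over 99% for an adjusted contrast on the affected samples. These figures rest on assumed effect sizes, correlation, equal variances and complete data. The structural point does not.

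The documents do not show that the sponsor intends a main-effects-only analysis.

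**What to change.** Replace the sentence with a model for calprotectin (transformed if skewed, as the plan already allows) that has group, categorical time and group-by-time interaction as fixed effects and subject as random effect. Adjust for the day 0 value, either as a covariate with the later samples as response or by constraining the groups to a common day 0 mean.

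Name one group contrast in advance as the test of the lysate effect, for example the average difference over the post-vaccine samples. Do not rely on the 7-df interaction F test, which loses power when the effect is sustained.

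The change costs a sentence or two of analysis text. Every sample needed is already scheduled. The one real commitment is to fix the contrast days before unblinding. A poorly matched choice costs something: averaging all six post-vaccine samples when only four carry a 1 SD effect gives a noncentrality of (4/6)/0.187 = 3.56 and about 93% power at correlation 0.5, still well above the 52% of the additive term.

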*Lactobacillus plantarum* is listed in the Korean Health Functional Food code [8] and is a representative probiotic that appears in the fermenting season among the lactic acid bacteria in Kimchi, a Korean traditional fermented food. Lipoteichoic acid (LTA), a component acquired from the cell wall, was considered a proinflammatory molecule of Gram-positive bacteria [9]. However, in several studies, LTA separated from beneficial bacteria such as *Lb*. *plantarum* showed weak nitric oxide production compared to pathogen and attenuated the induced inflammation [9–12]. Also, our previous study showed that *Lb*. *plantarum* K8 lysate regulated Toll like receptor-2 signaling, prevented DSS-induced intestinal mucosal damage, and reduced increased proinflammatory cytokines in rats [13]. Therefore, we expect *Lb*. *plantarum* K8 lysate to help regulate the balance of the intestinal immune system. However, the efficacy of *Lb*. *plantarum* K8 lysate on gut immunity in the general population has rarely been studied.

In this study, we aimed to develop a new human intervention study protocol that can be used to study gastrointestinal inflammation. Because of the immunogenicity of the cholera vaccine targeting the gut, we aim to provide support for our concept that, in addition to inducing a protective immune response, this vaccine might also be used as a safe approach to induce a mild gastrointestinal inflammatory response in healthy human subjects, as a challenge model for dietary intervention studies. To study whether this inflammatory response or the vaccination response can be modulated by an active ingredient, we use *Lb*. *plantarum* K8 lysate as an intervention.

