### Interventions

All subjects will receive the registered oral cholera vaccine Dukoral^®^ according to the standard vaccination scheme on visit 2 and visit 5 (2 doses, 14 days apart). Participants will take probiotic lysate material or a placebo for 6 weeks (day 1–43). Both products will be coated with identical colors and shapes and will be provided to the subjects in bottles. A daily serving consists of two chewable tablets, to be taken as one tablet twice a day.

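### The stated between-group model over days 1–43 does not isolate the lysate's effect on the vaccine-induced calprotectin response: it dilutes that effect and would mix in any resting effect

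*Protocol article*

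**What the plan says.** - **Question.** The Discussion states as second hypothesis that the "K8 lysate will significantly improve the inflammatory response or support the immune response induced by oral cholera vaccination". The target is a response that the vaccine provokes.
- **Analysis.** The Statistical analysis section names "A linear mixed-effects model with group and time as fixed effects and subject as the random effect", which "will be applied to compare the changes between groups over the intervention period". It lists no group-by-time term and no reference sample. It also lists paired and two-sample tests, without time points.
- **Period.** Under Interventions: "Participants will take probiotic lysate material or a placebo for 6 weeks (day 1–43". Under Outcome measures: "The vaccination time points are fixed on day 15 and day 29". Product days 1–14 are therefore free of vaccine.
- **No unchallenged arm.** Under Interventions: "All subjects will receive the registered oral cholera vaccine".
- **Stools.** Under Outcome measures: "Fecal samples will be collected on days 0, 14, 16, 17, 28, 30, 31, and 42". Days 14 and 28 are the day before each dose; days 16, 17, 30 and 31 are one and two days after a dose.
- **Primary outcome.** Fecal calprotectin (Abstract).

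**The concern.** A lysate effect on the vaccine response can show only in stools that follow a dose, judged against stools taken shortly before it. The stated model does not make that comparison. With group and time but no interaction, its only arm coefficient is one level difference held constant over all eight stools, including day 0, before any product is taken. Read more generously as an average change over the product period, it still gives the day 14, 28 and 42 stools the same weight as the four early post-dose stools.

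Two things follow. A true difference in vaccine response is averaged with stools where little or none is expected, so power falls. And if the lysate moves calprotectin by itself during the two vaccine-free weeks, that shift enters the same estimate and cannot be told apart from modulation of the challenge. The dilution needs no resting effect; the mixing does. What is at stake is the conclusion on the second hypothesis, and with it the claim that the vaccine model can show a dietary effect.

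**Working it through.** **Inputs from the protocol article.** Stool days 0, 14, 16, 17, 28, 30, 31, 42; vaccine on days 15 and 29; 23 per arm with 20% dropout, 23 × 0.8 = 18.4, taken as 18 completers; calprotectin 15 ± 20 µg/g (Sample size calculation). The sample size there rests on paired testing and gives no power for the lysate comparison, so there is no plan figure to reproduce for this contrast.

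**Assumptions.** Log-normal calprotectin, so log SD = √ln(1 + (20/15)²) = 1.01 (variance 1.022); equal correlation r between stools, 0.3 to 0.7; vaccine response confined to days 16, 17, 30 and 31. Let V be the arm difference in vaccine response and R the resting lysate effect from day 14 on, both in log units.

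**Step 1: what each quantity estimates.** The expected arm difference is 0 on day 0, R on days 14, 28 and 42, and R + V on days 16, 17, 30 and 31.
- Group effect over eight stools: [3R + 4(R + V)]/8 = (7/8)R + (1/2)V.
- Average change from day 0: [3R + 4(R + V)]/7 = R + (4/7)V.
- Mean of days 16, 17, 30, 31 minus mean of days 14, 28: (R + V) − R = V.

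**Step 2: power with no resting effect (R = 0, V = −0.5).** With balanced data the group effect compares subject means.
- Group effect: variance per subject 1.022 × [r + (1 − r)/8].
  - r = 0.3: 0.396, SE = √(2 × 0.396/18) = 0.210, ratio 0.25/0.210 = 1.19, power 21%.
  - r = 0.7: 0.754, SE 0.289, ratio 0.86, power 13%.
- Pre-dose to post-dose contrast: variance per subject 1.022 × (1 − r) × (1/4 + 1/2).
  - r = 0.3: 0.536, SE 0.244, ratio 0.5/0.244 = 2.05, power 51%.
  - r = 0.7: 0.230, SE 0.160, ratio 3.13, power 86%.

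These powers use the noncentral t with 34 degrees of freedom. Simulation gives 14–22% and 51–86%, the same within about a percentage point.

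**Step 3: if there were a resting effect (illustration only).** Take a 39% resting fall (R = −0.5; 1 − e^−0.5 = 0.39) and the same vaccine response in both arms (V = 0). The group effect is significant in 30–54% of trials and an overall group-by-time test in 17–39%. The pre-dose to post-dose contrast stays at about 5%, provided the vaccine multiplies calprotectin by the same factor in both arms. In the other direction, (7/8)R + (1/2)V is zero when R = −(4/7)V, so an opposite resting effect of that size hides V completely.

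**Step 4: does the contrast depend on scale?** Yes. Suppose the vaccine adds the same 15 µg/g in both arms. The log contrast then rejects falsely in 26–28% of trials for a 39% resting fall and in 46–49% for a 50% fall. The group effect as written is at 27–72% in those settings, and the untransformed contrast stays near 4%.

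**The case against.** **The contrast is not fixed, and details belong to the analysis plan.** The quoted phrase may only name the span of the repeated measures, an interaction may be understood, and the listed t-tests could be applied from day 14 to days 16 and 17. This stands in part: the article does not exclude a pre-dose comparison. But it does name one model for comparing change between arms, with its terms and period, and that model followed as written answers the second hypothesis poorly. Adding an interaction and testing it overall does not separate R from V either (Step 3).

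**A stronger reading is not supported.** A reader might infer that the lysate comparison is change from day 0, so that a resting effect will be declared to be modulation. The Statistical analysis section never names day 0 as reference, and no passage reports or quantifies a resting effect in healthy people. The Introduction does say that lipoteichoic acid "was considered a proinflammatory molecule of Gram-positive bacteria", but the next sentence goes the other way for beneficial bacteria such as *Lb. plantarum*, and the K8 evidence cited concerns chemically induced damage in rats. A resting rise in particular has little support.

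**Plasma markers.** Most already start at visit 2, with blood taken before the vaccine, so their first value is pre-dose. This stands; the point is about fecal calprotectin.

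**The alternative has weaknesses too.** Day 28 falls 13 days after dose 1 and may carry a residual response. If that response persisted in full, the contrast would return only V − V/2 = V/2. The log contrast also assumes a multiplicative vaccine response (Step 4). Both stand and shape the fix.

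**A wider aim.** The Study design section speaks of modulating local and systemic inflammation, which an over-period comparison does serve. It does not serve the narrower second hypothesis.

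**Conclusion.** The point holds for the primary outcome and the second hypothesis. The firm part is the dilution: weight 1/2 for a difference in vaccine response in the group effect, 4/7 in an average change from day 0. It costs power even with no resting effect: about 14–22% against 51–86% for a 0.5-log dampening. This assumes 18 per arm, log SD 1.01, equal correlations of 0.3–0.7 and a response confined to the four early post-dose stools; a longer-lasting response would lessen the dilution.

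The conditional part is the mixing. The 14 vaccine-free product days leave room for a resting effect to enter the estimate, and no arm is left unvaccinated to show it. Its size and direction are assumptions, so the 30–54% false-positive figure illustrates what could happen and does not forecast it. Nor is the pre-dose to post-dose contrast immune on every scale.

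**What to change.** In the Statistical analysis section:

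1. Add group-by-time to the mixed model. Define the lysate effect on the fecal vaccine response as the arm difference in (mean calprotectin on days 16, 17, 30 and 31) minus (mean on days 14 and 28), tested as one contrast.
2. Report the arm difference in change from day 0 to day 14 separately, as the resting effect of the product.
3. Give a sensitivity analysis with dose 1 only (day 14 to days 16 and 17), because day 28 may carry a residual dose-1 response. It uses fewer stools and is less precise.
4. Show the contrast on the log and the µg/g scale, and say beforehand how a disagreement will be read.
5. For plasma markers first measured at visit 2, use change from visit 2. Do not re-anchor the antibodies at visit 5, which would discard the dose-1 response.

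The cost is a few sentences and no new samples. One downside should be accepted openly: a general lowering of calprotectin on lysate will be reported as a resting effect and not as modulation of the challenge, and the conclusion will depend somewhat on scale.
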